### Who takes informed consent? {26a}

Eligible patient’s written informed consent is obtained by a trial investigator, in the presence of a witness, after clear and detailed information has been provided to the patient and before any trial procedure is carried out. Participation is voluntary, participants can withdraw at any time, and inclusion in the trial does not affect the patient’s usual care.

### Additional consent provisions for collection and use of participant data and biological specimens {26b}

Permission for serum banking is included in the informed consent. Patients are informed that their anonymised data might in the future be the subject of clinical research and they can oppose this by informing the investigator.

## Interventions

### Explanation for the choice of comparators {6b}

The choice of placebo as a comparator was made on the basis of the absence of any efficient and available drugs for the treatment of NAAION.

### Intervention description {11a}

The treatments are initiated after inclusion and randomisation according to the group to which the patient is assigned: Group 1: oral 125 mg bosentan twice a day (BD) (total dose, 250 mg/day); Group 2: oral placebo, BD. Treatments are administered for 8 weeks.

The coordinating pharmacy prepared the investigational medicinal products (IMP), obtained from Pharmascience Inc. Montréal, Québec. Masking of pms-BOSENTAN 125 mg and 62.5 mg tablets was done by overencapsulation in size #1 opaque capsules. Pms-BOSENTAN 125 mg placebo and pms-BOSENTAN 62.5 mg placebo are empty capsules overencapsulated in the same size #1 and colour opaque capsules. The coordinating pharmacy also performed the packaging and labelling of the IMP and matching placebo. Thus, IMPs and placebos are indistinguishable.

### Criteria for discontinuing or modifying allocated interventions {11b}

No adjustments in dosage according to age are planned, in line with the Summary of Product Characteristics (SmPC). A reduction in dosage is foreseen in case of any increase in liver transaminases (Table 3). The normal bosentan dosage can be resumed only if the level of transaminases has returned to their baseline value. Transaminase levels must be verified 3 days after resumption of bosentan, and then every 2 weeks. Similarly, a reduction in the dosage of bosentan (or its interruption) is planned in case of a sustained fall in systolic blood pressure (Table 3).

**Table 3 Tab3:** Algorithm for reducing dosage or discontinuation of bosentan depending on hepatic transaminases and systolic blood pressure

	Modification	Action to take
**Hepatic transaminase**		
> 3 and ≤ 5 × LSN	Reduce the daily dose by half (i.e. 62.5 mg morning and evening in this trial) and check transaminase level at least every 2 weeks.	If the level returns to its starting value, continue or resume bosentan treatment if applicable.
> 5 and ≤ 8 × LSN	Interrupt treatment and verify transaminase level at least every 2 weeks.	Once the rate has returned to starting value, resume bosentan treatment.
> 8 × LSN	Definitively interrupt bosentan treatment.	In case of high transaminase level with clinical signs of liver disorder (e.g. nausea, vomiting, fever, abdominal pain, jaundice or unusual lethargy or fatigue) or high bilirubin level equal to or greater than twice the LSN, bosentan treatment should be interrupted definitively.
**Systolic blood pressure**		
SBP < 100 mmHg		Re-verify BP at investigating centre
90< SBP < 100 mmHg		Verify BP the next day at investigating centre
Persistent 90< SBP < 100 mmHg		Self-measurement verification of BP every week until normalisation
SBP < 90 mmHg	Reduce dose (bosentan/placebo 125 mg) by half to (bosentan/placebo 62.5 mg)	Check SBP for 3 days by self-measurement = medical verification of self-measurement results (patient brings device to hospital)
		SBP < 90 mmHg = discontinue treatment
		SBP > 90 mmHg = continue half dose
SBP < 90 mmHg more than 20 mmHg lower than SBP compared to screening	Immediately reduce dose of (bosentan/placebo 125 mg) by half (bosentan/placebo 62.5 mg)	Monitor BP for 3 additional days with self-measurement after dose reduction, then medical verification of self-measurement results (patient brings device to hospital)
		If hypotension SBP < 90 mmHg is maintained: discontinue treatment
		If SBP > 90 mmHg = continue half dose

*LSN* last seen normal

Participant withdrawal may be at the request by the patient and/or due to a severe adverse event. Furthermore, the patient’s participation in the study can be discontinued if liver enzymes exceed five times the upper limit of normal. After discontinuing the treatment, patients are seen in consultation every 2 weeks until the disappearance of their abnormal liver enzyme levels. Subjects who have withdrawn or been withdrawn from the trial are not replaced. Consequently, a greater number of subjects will be included than required by the sample size calculation.

The sponsor can stop the study at any time for the following reasons: inability of the investigators to include patients in accordance with the planned timeline, absence of signed informed consent, major violations of the protocol or incomplete or erroneous data.

In case of an adverse event deemed by the investigator to be serious and that could harm their patients’ health, the investigator can stop their participation in the study with the agreement of the sponsor.

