### Sample size {14}

The sample size calculation was based on VF data (primary outcome) from a published study [61], and from a retrospective analysis of the patient cohort at Grenoble-Alpes University Hospital (personal data). Bellusci et al. [61] showed that inferior VF defects varied from −11.7 ± 2.7 at diagnosis to 10.3 ± 3 dB (*n* = 5) at 6 months, with diffuse defects varying from −15.5 ± 7.4 to −16.4 ± 7.9 dB (*n* = 7) and central defects varying from −5.3 ± 0.7 to 4.8 ± 1.7 dB over the same timespan (*n* = 4). Consistently, in our retrospective cohort, the progression of inferior altitudinal VF defects (*n* = 14) showed an 11% deterioration in the mean deviation (MD) between 3 and 6 months (from −15.2 ± 9 initially to −15.8 ± 7.8 dB) and 21% worsening of the MD for superior altitudinal defects (*n* = 8, from −14.9 ± 4.2 dB initially to −17.08 ± 5.7 dB).

We hypothesised that the mean deviation at inclusion would be −15 ± 9 dB and that the treatment would provide a 40% improvement in the defect, i.e. a progression from −15 to −9 dB, while no change is expected in the placebo arm. A sample size of 36 patients per group would thus provide 90% power to detect such a difference using a general linear model, with a common standard deviation of 9, an alpha risk of 0.05 and with an *r*-squared for the covariate (VF at baseline) of 0.3. To take account of patients lost to follow-up and/or those with prematurely stopping the protocol (including interruptions related to the side effects of bosentan, evaluated at 20% of the sample, *n* = 14), a total of 86 patients need to be included (*n* = 43 per group).

This sample size should provide >90% power to detect a significant difference in the thinning of retinal nerve fibres, hypothesising a smaller reduction in RNFL thickness after treatment (reduction evaluated at −43% in the placebo arm patients versus −25% in patients treated with bosentan), using an ANCOVA.

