## Statistical methods

### Statistical methods for primary and secondary outcomes {20a}

Data from all patients included in this study will be included in the final analysis, following the modified intention to treat (mITT) principle. Data may be excluded from the analysis if an automated VF assessment was not obtained and/or VF parameter values are not reliable.

The number of patients presenting a major deviation to the protocol will be listed, and a sensitivity analysis on the per protocol population will be conducted. The major deviations will be reviewed by the trial’s data and safety monitoring board (DSMB).

The quantitative variables will be presented as means and standard deviations. The qualitative variables will be presented as numbers and percentages. Statistical analysis will be performed using STATA® Software Version 14.2 or higher (Stata Corporation [name]). Data normality will be evaluated graphically and tested using the Shapiro-Wilk test. The statistical tests will be interpreted considering a two-sided *p*-value < 0.05 as significant.

For the *primary endpoint analysis*, the progression in the MD (in decibels) of the VF between baseline (inclusion visit, D1) and the 3-month visit (M3) measured using automated perimetry, i.e. delta M3 – D1, will be compared between the two groups using a linear mixed effects model, with the group as a fixed factor. The study centre will be included in the model as a random effect, and the MD at baseline will be included as a covariate in the model.

A second model of the same type will be built, adjusted on the presence of OSAS and on other baseline parameters that potentially differ between the two groups (here the *Y* variable will be the difference in RNFL: M3 – D1). The quantitative variables will be log-transformed if their distribution is not normal, so as to satisfy the conditions required to apply linear models.

For the *secondary endpoint analyses*, the same type of analysis as that used for the primary endpoint will be used for VA. Other comparisons between the two groups will be made using the Student *t* test or the Mann–Whitney *U* test (depending on the normality of the data distribution) for quantitative variables. Qualitative variables will be analysed using the chi-squared test (or the Fisher exact test depending on the theoretical number of patients).

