### Methods in analysis to handle protocol non-adherence and any statistical methods to handle missing data {20c}

All available data will be included in the final mITT analysis, even in case of protocol non-adherence. However, missing data will not be replaced.

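### The protocol lets toxicity end study participation, not only treatment, and does not say that the month-3 visual field is still obtained; any liver-triggered loss would fall mainly on bosentan

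*Protocol article*

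**What the plan says.** All sections cited are in the protocol article.

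- **{11b}, text under Table 3.** "Participant withdrawal may be at the request by the patient and/or due to a severe adverse event". Also, the patient's "participation in the study can be discontinued if liver enzymes exceed five times the upper limit of normal". After treatment is stopped, "patients are seen in consultation every 2 weeks until the disappearance of their abnormal liver enzyme levels". Withdrawn subjects are not replaced; more patients are enrolled instead.
- **{11b}, Table 3.** Above 5 and up to 8 times, treatment is interrupted and resumed once the level is back to its starting value. Above 8 times, bosentan is stopped for good. If systolic pressure stays below 90 mmHg, treatment is discontinued. Each of these entries acts on treatment; none mentions participation.
- **{14}.** The allowance of 14 patients is for ordinary loss to follow-up and also for "those with prematurely stopping the protocol (including interruptions related to the side effects of bosentan, evaluated at 20% of the sample".
- **{20c}.** "All available data will be included in the final mITT analysis, even in case of protocol non-adherence". Missing data are not replaced.
- **{13}.** Ophthalmological visits run to 24 months. The section does not say whether they continue for a patient withdrawn for toxicity.

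**The concern.** Stopping the capsules and leaving the study are different events, and only the second costs the trial its outcome data. The text under Table 3 allows the second on toxicity grounds. For patients who stop treatment it names only a liver safety visit, which ends when the enzymes normalise.

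The Discussion calls liver dysfunction the most significant side effect of bosentan, so loss through this route would be expected mainly in the active arm. The patients concerned have had a shortened course. If their month-3 fields are never taken, the bosentan mean rests on patients who tolerated the drug somewhat better than the arm as randomised, and the comparison can lean towards bosentan. The 24-month bilateralisation rate would lose the same patients. Fields that were never taken cannot be recovered at analysis.

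**Working it through.** **1. The passages side by side.** Above five times the limit, the text allows participation to end. Table 3, for part of that same range, plans for study treatment to resume. A patient removed from the study cannot resume study treatment, so the two must be reconciled. (Table 3 counts in multiples of LSN, which its footnote expands as last seen normal; the comparison takes this to be the same scale as the upper limit of normal.) Section {20c} keeps non-adherent patients if they have data, but a withdrawn patient produces none.

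**2. The plan's own sample size.** Inputs from {14}: difference 6 dB (−15 to −9 against no change), SD 9, r² = 0.3, "an alpha risk of 0.05", power 90%. Two-sided testing is from {20a}.

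n per group = 2 × (1.960 + 1.282)² × 9² × (1 − 0.3) / 6² = 33.1, so 34. With the noncentral t distribution, 34 per group give 89.9%, 35 give 90.7% and 36 give 91.5%. The stated 36 is reproduced to within two patients. Total: 72 + 14 = 86, or 43 per arm.

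**3. Patients at risk.** The documents give no rate above five times. The Discussion brackets it, as an assumption:

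| Source figure | Rate | Of 43 bosentan patients |
|---|---|---|
| Above 8 times, placebo-controlled study (read as a share of all patients) | 3.0% | 1.3 |
| Bosentan interrupted for aminotransferase rise | 3.2% | 1.4 |
| Above 8 times, longer observational study | 4.2% | 1.8 |
| Above 3 times, lower figure | 9.7% | 4.2 |
| Above 3 times, upper figure | 14.9% | 6.4 |

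This gives about 1 to 6 patients. Liver-triggered loss on placebo is assumed to be near zero.

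**4. Bias in the bosentan mean.** With a share f of the arm lost,

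bias = f × (mean change of retained − mean change of lost).

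The gap is not known. A gap of 6 dB means that those lost would have had none of the planned benefit; 3 and 9 dB show the range.

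| Lost of 43 | Gap 3 dB | Gap 6 dB | Gap 9 dB |
|---|---|---|---|
| 1 | 0.07 | 0.14 | 0.21 |
| 4 | 0.28 | 0.56 | 0.84 |
| 6 | 0.42 | 0.84 | 1.26 |

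Example: 4/43 × 6 = 0.56 dB.

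**5. Why a larger sample does not help.** As a stress test, if all 14 allowed losses fell on bosentan (29 against 43), power for 6 dB would still be 90.5%. The allowance protects power. It does nothing about which patients are missing.

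**6. Power if these patients are kept.** Suppose that those who stop get no benefit and all 43 per arm are analysed. The difference is then 6 × (1 − f):

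| Stop rate | Difference | Power |
|---|---|---|
| 0% | 6.00 dB | 95.5% |
| 3.2% | 5.81 dB | 94.2% |
| 10% | 5.40 dB | 90.8% |
| 14.9% | 5.11 dB | 87.4% |

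**The case against.** The strongest reply is that the protocol contains no rule that toxicity ends participation. The wording is permissive throughout, and the Table 3 entries act on treatment. Section {13} schedules fields to 24 months with no exemption for patients off treatment, {20a} includes all patients in the mITT analysis, and {20c} keeps those who did not adhere. The full protocol may say more than the article. The directly relevant figure, 3.2% of patients interrupting bosentan for aminotransferases, implies 0.032 × 6 = 0.19 dB even if all were lost and had gained nothing.

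Much of this stands, and it limits the point. A reader might infer that toxicity as such takes patients out, so that the mITT comparison becomes one of patients who tolerated the drug. The documents do not support that: the text permits withdrawal without requiring it, and the expected numbers are small. Nor do they support three further steps:

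- **Loading the whole 20% onto bosentan** (0.20 × 6 = 1.2 dB). The allowance also covers ordinary loss to follow-up, and no split by arm is given.
- **Treating every rise above three times as a trigger.** The participation sentence starts above five times, and Table 3 reduces the dose at 3 to 5 times. The 7.6% post-marketing figure has no stated threshold.
- **Extending the imbalance to all severe events.** Table 6 shows rates close to placebo for several effects, such as headache (11.5% against 9.8%).

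What does not stand is that the visit schedule and the mITT rule settle the matter. Neither supplies data for a patient whose participation has ended, and permissive wording leaves loss of the primary outcome to each site. The conflict at above five times lies within the published text, so it is not a matter of condensed detail.

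**Conclusion.** The point holds as a contradiction and a gap in outcome collection. Followed as written, the plan can lose month-3 fields through a known effect of the active drug. The wording of {14} suggests that such patients are expected to be lost to the analysis, although it does not say so outright.

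The plausible bias is about 0.14 dB (1 patient lost) to 0.84 dB (6 lost) on a planned 6 dB, and 0.07 to 1.26 dB over the whole range of assumed gaps. The lower end is more likely: the trigger is above five times, the reported liver-stop rate is 3.2%, and treatment lasts only 8 weeks.

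This rests on three assumptions: a rate above five times lying between the reported figures, little liver-triggered loss on placebo, and lost patients doing worse than retained ones. The 6 dB gap supposes that bosentan works as planned. If it has no effect, a shortened course costs nothing, and bias arises only if liver toxicity is linked to visual prognosis.

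**What to change.** 1. In {11b}, reconcile the sentence on five times the upper limit of normal with Table 3. Which clinical rule should apply is for the sponsor and investigators.
2. Separate stopping study treatment from stopping outcome collection. State that patients who stop treatment for any reason are still asked to attend the scheduled visits, with the month-3 field first and then months 6, 12 and 24, unless they withdraw consent to follow-up. This does not restrict decisions made on safety grounds.
3. State that these patients are analysed in the mITT population.
4. In {14}, stop treating side-effect interruptions as lost outcomes by default.

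**Cost.** A wording amendment and a note to sites; the visits are already in the schedule. The estimated effect may be somewhat smaller, because shortened courses are included. Power stays above 90% at stop rates of 3.2% and 10%, and falls to about 87% at 14.9%. The reach is limited: with 72 of 86 patients included and 49 through full follow-up, only those still in follow-up or yet to be enrolled can benefit, and for the month-3 field only those who have not passed that visit.

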### Strategies to improve adherence to interventions {11c}

The importance of good adherence to the study treatment is explained to the patient at the screening and inclusion visits. No other direct measures are being taken to improve adherence.

### Relevant concomitant care permitted or prohibited during the trial {11d}

As far as possible, introducing, or modifying existing, concomitant treatments should be avoided throughout the trial.

The prescription of aspirin at a dosage of between 75 and 300 mg/day is tolerated if it is indicated for cardiovascular disorders in secondary prevention for patients with a history of complicated carotid or coronary atheroma, stroke, arteriopathy of the lower limbs or aneurism of the abdominal aorta. In primary prevention, aspirin will be proposed starting in the 3rd month of the protocol, after discontinuing bosentan or placebo treatment. If necessary, continuous positive airway pressure (CPAP) treatment can be initiated after the visit at 3 months.

Simvastatin treatment requires adapting the dosage to the patient’s lipid profile (cholesterol level), given that bosentan reduces the plasma concentrations of simvastatin. Prohibited treatments or those requiring close monitoring, as well as the related risks, are summarised in Table 4.

**Table 4 Tab4:** Prohibited treatments or those requiring close monitoring

**Prohibited treatments**	**Risks**
Cyclosporine A	Major risk of increasing residual plasma levels of bosentan following transport protein inhibition of bosentan in hepatocytes
	Major risk of decreasing plasma concentrations of cyclosporine with reduction in its efficacy and therefore its immunosuppressive activity
Glibenclamide	Major risk of increasing risk of elevation of liver enzymes
General corticosteroid therapy	Risk of interfering with potential efficacy of bosentan
Amiodarone	Drug giving NAAION-like picture
CYP 3A4- and 2 C9 2C19-inhibitor drugs	Risk of increasing plasma bosentan concentrations
CYP 3A4-, 2C9-inductor drugs	Risk of decreasing plasma bosentan concentrations
Protease- and ritonavir-inhibitor drugs	Risk of increasing plasma bosentan concentrations
Nevirapine	Pronounced hepatotoxicity that can potentially cumulate with that of bosentan.
**Not recommended**	**Close monitoring required**
Anti-coagulants (warfarin and other antivitamin Ks)	INR (3–4 days after beginning of treatment, after each dosage modification and after discontinuation of bosentan treatment) during treatment initiation and/or dosage increase
Hormonal contraceptives (oestrogen/progestin combination and progestin-only pills)	Risk of reducing efficacy
Sildenafil intake	Discontinuation of this drug should be discussed with the patient to be included in the protocol, especially since sildenafil is suspected of being associated with NAAION onset.
Immunosuppressors (tacrolimus and sirolimus)	Bosentan lead to increase in the concentration of tacrolimus and sirolimus

*INR* international normalised ratio, *NAAION* nonarteritic anterior ischemic optic neuropathy

### Provisions for post-trial care {30}

After the end of follow-up, patients receive normal care appropriate to the progression of their condition. If there are any harms due to trial participation, compensation is included in the assurance cover take out by the sponsor.

### Outcomes {12}

The *primary endpoint* (a) is the mean deviation in VF (in dB) 3 months after inclusion. This endpoint is considered sufficient to assess functional and anatomic recovery with the disappearance of optic disc swelling by this time [57].

The *secondary endpoints* are as follows: (b) peripapillary retinal nerve fibre thickness (RNFL) and macular ganglion cell layer thickness measured using SD-OCT at 3, 6, 12 and 24 months after inclusion; (c) visual function (VA using the ETDRS scale and VF) at 6, 12 and 24 months: (d) the extent of bilateralisation of NAAION at 24 months; and (e) quality-of-life parameters assessed using the visual function questionnaire (VFQ-25) [58] at 3 and 12 months.

### Participant timeline {13}

The timeline for inclusion, assessments and visits for the participants are summarised in Fig. 2. Patients are seen in consultation to evaluate tolerance (including blood tests), adherence and treatment efficacy at 2 weeks, 1 month, 2 months and 3 months).

**Fig. 2 Fig2:**
[figure not shown]
Schedule of enrolment, interventions and assessments for a patient included in the ENDOTHELION trial

Following randomisation, the first administration of the treatment is given in the ophthalmology department. Blood pressure (BP) is checked 4 h after this, corresponding to the plasma peak of bosentan according to the pharmacological data in the study by Weber et al. [59].

Patient monitoring/follow-up includes consultations at week 2, and at 1, 2, 3, 6, 12 and 24 months with one of the investigating ophthalmologists, during which several examinations are carried out: an ophthalmological examination (VA, VF, SD-OCT and fundus examination), a clinical examination searching for the adverse side effects of bosentan, an office-measurement of BP and a blood work-up including a haemogram and measurement of liver enzymes (until and including the month 2 visit). Self-measurement of BP is programmed during weeks 1 and 4 and the last week of treatment (week 8).

The primary endpoint is set at 3 months so as to assess the efficacy of bosentan before initiating treatment for OSAS, the recognised period when visual function usually stabilises, and papillary oedema disappears, proceeding to papillary atrophy. Contreras et al. [60] showed that at 1.5 months following the acute phase, the RNFL thickness of the affected eye was similar to that of the unaffected eye, indicating that the optic disc swelling had partly resolved. After this first period, atrophy of the optic nerve head became detectable, such that at the 3-month visit, the RNFL had thinned by 39%, compared to the contralateral normal eye [60]. Loss of retinal nerve fibre layers stabilised thereafter, with only 6% additional thinning at the 12-month visit. In another study, Hayreh et al. [57] estimated the median time to papillary oedema resolution was 7.9 weeks (IQR, 5.8–11.4 weeks).

In the present trial, at 3 months, the clinical examinations and laboratory analyses (including a study of endothelial function), the ophthalmological examinations (VA, VF, SD-OCT and fundus examination) and the blood work-up (with serum banking) performed at inclusion are repeated. A polysomnography is planned after the 3-month visit.

The visits at 6 and 12 months and the end-of-protocol visit at 24 months include an ophthalmological examination (VA, VF, SD-OCT and fundus examination). The quality-of-life questionnaire (VFQ-25) [58] is completed at the 3- and 12-month visits.

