### Objectives {7}

The *primary objective* of this trial is to compare the outcomes after 8 weeks of oral bosentan treatment vs. placebo, evaluated by changes in the automated visual field parameters at 3 months. The 3-month timeframe was chosen to assess both functional and anatomic evolution (resolution of optic disc swelling) [55].

The *secondary objectives* are to compare the peripapillary retinal nerve fibre thickness (RNFL) at 3, 6, 12 and 24 months after inclusion, visual function, i.e. visual acuity (VA) and visual field (VF), at 6, 12 and 24 months, quality of life at 3 and 12 months, inflammation markers and plasma levels of pre-proendothelin at 3 months, as well as the extent of bilateralisation of NAAION at 24 months, between the two groups (bosentan and placebo) of patients.

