### Eligibility criteria {10}

NAAION is diagnosed based on the standard criteria of recent (≤ 21 days), rapid and painless onset of VF loss, occurring with diffuse or sectorial swelling of the optic disc [56]. The trial’s inclusion and non-inclusion criteria are listed in Table 2. In each participating centre, possible differential diagnoses are carefully assessed by physicians with expertise in neuro-ophthalmology.

**Table 2 Tab2:** Inclusion and non-inclusion criteria

Inclusion criteria	Non-inclusion criteria
Age ≥ 50 years old	Pregnant or breast-feeding women^a^
Patients who signed the consent form	Patients with other acute or chronic intercurrent ocular pathology interfering with visual acuity or visual field (diabetes, drug-induced or other retinopathy, other optic neuropathy including uni- or contralateral glaucoma and/or intraocular pressure > 30 mmHg, advanced cataract, corneal opacities, amblyopia < 5/10, severe myopia > −6 diopters, retinal disease)
Patients affiliated with a national health insurance scheme or beneficiaries of such a scheme.	Simultaneous bilateral NAAION, occurring 1 month apart or less
	Evidence or suspicion of other causes of optic neuropathies considered as main differentials: 1/ giant cell arteritis causing arteritic anterior ischemic optic neuropathy (AAION) 2/ Optic neuritis (based on clinical examination, personal history of multiple sclerosis, contributive ancillary investigations) and 3/ compression/infiltration of the optic nerves, based on the clinical findings and orbital/brain imaging.
	Patients with systolic blood pressure below 100 mmHg
	Patient with orthostatic hypotension (20 mmHg drop in SBP and/or 10 mmHg drop in DBP when moving to a standing position)
	Neurological history of vascular or tumour-related changes to the visual field or other optic neuropathy
	Systemic inflammatory disease
	Known allergy to bosentan
	Patients with moderate to severe hepatic impairment (Child-Pugh class B or C), biliary cirrhosis (serum levels of liver aminotransferases, aspartate aminotransferases (ASAT) and/or alanine aminotransferases (ALAT), greater than three times the upper limit of normal, bilirubin greater than twice normal)
	Estimated glomerular filtration rate (GFR) < 30 ml/min/1.73 m^2^
	Patients treated with drugs whose efficacy may be reduced by activation of cytochrome P450, 2C9, 3A4 and 2C19 isoenzymes
	Patients treated with amiodarone

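### The VFQ-25 is assigned to an unadjusted t or Mann–Whitney test and the text shows no inclusion score, so precision is given away; the primary endpoint's type of model, with inclusion values, should be used instead

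*Protocol article*

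**What the plan says.** Three places in the protocol article set the times of the questionnaire. Objectives {7} has "quality of life at 3 and 12 months". Outcomes {12} has "quality-of-life parameters assessed using the visual function questionnaire (VFQ-25) [58] at 3 and 12 months". Participant timeline {13} has "The quality-of-life questionnaire (VFQ-25) [58] is completed at the 3- and 12-month visits".

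The same timeline section describes month 3 as a visit at which "the ophthalmological examinations (VA, VF, SD-OCT and fundus examination) and the blood work-up (with serum banking) performed at inclusion are repeated". The VFQ-25 is not in that list. The complete schedule is left to a figure: "The timeline for inclusion, assessments and visits for the participants are summarised in Fig. 2".

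Statistical methods {20a} gives the primary endpoint a mixed model with group as fixed factor, centre as random effect and baseline mean deviation (MD) as covariate. For the secondary endpoints, "the same type of analysis as that used for the primary endpoint will be used for VA". For the rest, "Other comparisons between the two groups will be made using the Student" t test or the Mann–Whitney test. The VFQ-25 falls in this last class.

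**The concern.** The VFQ-25 is the trial's quality-of-life endpoint, and as written it is compared on raw follow-up scores. Differences between patients that existed before treatment then stay in the error term. Centre, which stratifies the randomisation, is also left out for this endpoint although it is in the primary model.

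The plan does not work this way elsewhere. Its sample size for MD depends on baseline adjustment, and visual acuity (VA) receives the same type of model. With about 36 analysable patients per arm, an unadjusted comparison has little precision to spare. Without an inclusion score, change from inclusion cannot be reported either.

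**Working it through.** **The plan's own figure.** Inputs from Sample size {14}: difference 6 dB (−15 to −9), SD 9 dB, covariate r-squared 0.3, alpha 0.05 (two-sided, from {20a}), power 90%.

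- Adjusted SD = 9 × √(1 − 0.3) = 7.53 dB.
- n per arm = 2 × (1.96 + 1.28)² × 7.53² / 6² ≈ 33.1, so 34. With the t distribution it is 35. The stated 36 is reproduced to within two patients.
- Without the covariate: 2 × (1.96 + 1.28)² × 9² / 6² ≈ 47.3, so 48.

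Baseline adjustment is therefore what allows 36 per arm rather than 48 for the primary endpoint.

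**The same reasoning for the VFQ-25.** The documents give no SD, target difference or correlation for it. Results are in SD units, and the correlation r between covariate and outcome is assumed to be 0.3 to 0.7. Adjustment multiplies the standard error by √(1 − r²).

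The smallest difference detectable with 80% power at 36 per arm, unadjusted, is (1.96 + 0.84) × √(2/36) = 0.66 SD (normal approximation). Power below is for a true 0.5 SD difference, from the noncentral t distribution; unadjusted it is 55%.

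| r | Fall in SE | Detectable difference (80% power) | Power at 0.5 SD |
|---|---|---|---|
| none | – | 0.66 SD | 55% |
| 0.3 | 5% | 0.63 SD | 59% |
| 0.4 | 8% | 0.61 SD | 63% |
| 0.5 | 13% | 0.57 SD | 68% |
| 0.7 | 29% | 0.47 SD | 83% |

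The adjusted rows suppose that every analysed patient has the covariate. If the plan's r-squared of 0.3 for MD were borrowed (r = 0.55), the standard error would fall by 16%.

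**Adding the questionnaire at inclusion now.** Recruitment {15} gives 72 of 86 patients recruited, so at most 14 could supply an inclusion score: 14/86 = 16%. If those are adjusted and the other 84% are not, the information relative to no adjustment is 0.837 + 0.163/(1 − r²).

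- r = 0.4: 1.03, power 57%.
- r = 0.7: 1.16, power 61%.

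Both are against 55% unadjusted. The larger gains in the table are no longer attainable by this route.

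**Covariates already collected.** Plans for assessment and collection of outcomes {18a} has the visual field measured at inclusion in both eyes. The month-3 description in {13} shows that VA was also examined at inclusion. These values can serve as covariates for patients already enrolled. Their correlation with the VFQ-25 is not in the documents, so their gain can only be read from the assumed range.

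**The case against.** The strongest objection is that absence of an inclusion VFQ-25 is inferred from silence. Objectives {7} and Outcomes {12} also list retinal nerve fibre thickness, VA and visual field by follow-up times alone, yet those have inclusion values. By that convention, months 3 and 12 need not rule out a baseline. The schedule is in Fig. 2, which could not be read here. This stands. A reader might infer that the questionnaire is never given at inclusion; the text points that way, most clearly in the timeline section, but does not say so.

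A reader might also infer that the comparison is biased or that nothing can be done at analysis. Neither is supported. Randomisation keeps the between-group differences at months 3 and 12 valid, change from month 3 to month 12 can still be formed, and inclusion visual field and VA are available as covariates.

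A further argument would be that patients with earlier damage to the other eye depress the scores, since Table 2 rules out only "Simultaneous bilateral NAAION, occurring 1 month apart or less". That is uncertain: Table 2 also excludes other optic neuropathy, section {18a} speaks of the fellow eye as healthy, and no figure shows how many such patients enter. The point does not need it.

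Finally, this is a secondary endpoint with no power claim, and its objective is a between-group comparison, not change. That limits the weight of the point but does not remove it: {20a} assigns the unadjusted test whether or not an inclusion score exists. The mixed model in Methods for additional analyses {20b} does not supply the adjustment either, because it concerns progression after month 3 by sleep-apnoea treatment.

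**Conclusion.** The point holds as a minor one about precision. As written, the VFQ-25 is compared without baseline or centre, while the primary endpoint and VA have both, and the text shows no inclusion score. With complete covariate data the standard error would be 5% to 29% smaller for an assumed r of 0.3 to 0.7. That range is an assumption, and inclusion MD and VA may sit anywhere in it or below it. The 36 per arm is the plan's evaluable number; with fewer losses it could approach 43, where the unadjusted detectable difference would be 2.80 × √(2/43) = 0.60 SD. Whether an inclusion VFQ-25 exists remains open until Fig. 2 is checked.

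**What to change.** 1. Check Fig. 2 for an inclusion VFQ-25, and make Objectives {7}, Outcomes {12} and Participant timeline {13} state the answer.
2. If it is collected, amend {20a} so that months 3 and 12 are analysed with the primary type of model: group, centre and inclusion VFQ-25 score.
3. If it is not collected, use the same model on the score at each visit, with inclusion MD and VA (both eyes where measured) as covariates. Fix this before unblinding. Report between-group differences at months 3 and 12, not change from inclusion.
4. Adding the questionnaire at inclusion for the remaining patients, at most 14, is optional. Such a score should not be the model covariate: {20c} does not replace missing data, so most patients would drop out of the analysis.

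The cost is a minor amendment and slightly more analysis work, with no new patient data for step 3. One detail needs a sentence: {18a} allows Goldmann perimetry where automated perimetry is not feasible, so some patients may lack an inclusion MD, and the plan should say how they stay in the VFQ-25 model.
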